### Recruitment

#### Recruitment for feasibility study

Recruitment will be a two-stage process. The first stage will be the recruitment of the care homes. The research team will make contact with independent care home providers in North London and Northern Ireland to ensure that a broad range of care homes are recruited. The feasibility study will be conducted in 12 care homes (with expected 50% recruitment rate, 24 homes will be approached).

Eligible care homes will be informed about the study through the standard communication routes (letter/email/phone call or in person) and in collaboration with the Clinical Research Networks in London (North Thames and North West London), and with the South Eastern Health and Social Care Trust in Northern Ireland. The ENRICH network (https://enrich.nihr.ac.uk/pages/research-ready-care-home-network) will also be utilised to assist with recruitment. If eligible care homes want further information, a member of the research team will arrange a visit in person to provide the care home managers with an information sheet, further discuss the study and answer any questions about participation. At least 48 hours after discussing the study, eligible care homes will be contacted by the researcher to confirm whether they would like to take part or not.

The second stage will be the recruitment of eligible residents in participating care homes. The aim is to recruit approximately 10 residents per home. A minimum of five and a maximum of 20 participants will be recruited at each care home. For larger care homes, the research team will randomly select a sample of potentially eligible participants. A screening process comprising of three steps will determine eligibility. In step one, the care home manager will identify potentially eligible residents from their personal information stored in the care home records. The care home manager will then pass the names of residents who meet the following criteria to the research assistant: aged 65 years or over, live in the care home full time, not receiving end-of-life care or palliative care, have a good working level of oral English and are currently not taking part in another oral health intervention or programme. Potentially eligible residents will then be given a participant information sheet (PIS) by the care home manager for the two further eligibility tests (as these warrant separate consent). Once consent is obtained (at least 48 h later) for the two further eligibility tests, the research assistant will undertake the 6-CIT test (step two). Residents with normal cognitive function (6-CIT score of 0-7) and those with mild cognitive impairment (6-CIT score of 8-9) will be potentially eligible for inclusion in the study.

In step three, the research assistant will confirm whether the residents are dentate or partially dentate, by performing a brief dental check, known as ‘lift-the-lip’ exercise. If eligible, the research assistant will provide a PIS for the feasibility study and after at least 48 h will ask the resident to complete the informed consent form for the feasibility study (see ‘Who will take informed consent?’ section).

#### Process evaluation—recruitment for semi-structured interviews

In order to assess the intervention’s feasibility and acceptability, a researcher will approach and invite care home staff (managers, carers and others) and residents already enrolled in the study to take part in a semi-structured interview. A purposive sampling frame will be used to ensure a diversity of staff members are recruited. Those interested in taking part will be provided with a PIS. All potential participants will be given at least 48 h from discussing the study with the researcher to decide whether or not they wish to take part.

#### Cost-consequence model—recruitment for semi-structured interviews

Staff (managers, carers and other staff), residents and family members from included care homes will be approached and invited to take part in a semi-structured interview. Policymakers and key stakeholders, such as members of the Health and Social Care Board in Northern Ireland, National Health Service (NHS) Clinical Commissioning Groups, the Care Quality Commission, the Regulation and Quality Improvement Authority (Registration and Inspection Unit in Northern Ireland), PHE and third sector organisations on ageing, will be approached to arrange a meeting or telephone call to discuss the study and provide input.

A purposive sampling frame will be used to ensure a diverse sample is recruited. Those interested in taking part will be provided with a PIS. All potential participants will be given at least 48 h from discussing the study with the researcher to decide whether or not they wish to take part.

### Assignment of interventions: allocation

#### Sequence generation

Eligible care homes will be randomised (via North Wales Organisation for Randomised Trials in Health Clinical Trials Unit, NWORTH CTU) at site level based on a 1:1 ratio (six interventions and six controls). Research assistants at each site will inform the NWORTH CTU when there are two eligible care homes. Care homes will be randomised in pairs, using a dynamic adaptive randomisation algorithm [33]. Care homes will be stratified by geographical location (North London/Northern Ireland).

#### Concealment mechanism

Randomisation will be at care home level. Once care homes have been entered into the system an independent NWORTH member of staff will allocate the homes using a dynamic adaptive randomisation algorithm [33].

#### Implementation

Since this is a cluster feasibility trial, participants will be allocated to the treatment that has been assigned to the care home. An independent NWORTH member of staff will allocate the care homes and a research assistant will enrol participants on to the study.

### Assignment of interventions: Blinding

#### Who will be blinded

Due to the nature of the intervention, the blinding of care homes and residents is not feasible. However, the clinical dental examiners that will record the baseline and outcome measures will be. The care home staff will be instructed not to reveal allocation information to the dental examiners. The study statistician will be blinded to allocation and will be unblinded after primary analysis has been completed.

#### Procedure for unblinding if needed

The study design is open label with only the statistician being blinded. The statistician will be unblinded to allocation only after all the data have been collected, entered into the database, cleaned and primary analysis has been completed.

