### Who will take informed consent?

For the two eligibility tests (6-CIT and brief dental check), written informed consent will be obtained from care home residents by a research assistant. For the feasibility study, written informed consent will be obtained from eligible care home residents by a research assistant or dental examiner. A research assistant will also take written informed consent for the interviews undertaken as part of the process evaluation and cost-consequence model. Written informed consent will be taken at least 48 hours after informing the participants about the study.

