A care home staff training package (containing a training video and hard copy training manuals and laminated reference guides, as well as online training through a dedicated website as described above) to facilitate appropriate knowledge and skills to implement oral health promotion activities. Care home staff will be required to undertake formal training to support the residents’ oral health prior to the residents completing the baseline assessments. The training will be overseen by the care home manager and the research team, and will be added to the log of mandatory training. Following the initial training prior to baseline assessments, care home staff will have access to the training package online at anytime during the study. The turnover rate of employed staff working in the UK care sector is high; it is therefore probable that a change in care staff involved in the study will occur. As a result of this, the training package will also be part of the induction training for new staff members.Administration by trained care home staff of OHAT, a brief and practical assessment of the resident’s oral health needs that is reviewed and updated over time. Administration will take place immediately prior to the initial dental assessment at baseline and at the 12-month follow-up visit. Care home staff will also be asked to complete a ‘Personal Oral Care Plan’ for each resident following completion of the OHAT, and will be asked to update it after reassessment of the OHAT or after any dental visit.A ‘support worker assisted’ daily tooth-brushing regime with toothpaste containing 1500 ppm fluoride (provided by the study). This will involve care home staff brushing the teeth of residents who have problems with their oral self-care or providing assistance to those residents who are able to brush their own teeth. This may include reminders to brush their teeth as well as guidance on brushing appropriately. Tooth brushing will be undertaken twice daily, once in the morning and once in the evening. To facilitate this, a guide on how to deliver oral care will be provided in the form of a poster and ‘Tips and Tricks’ cards. These ‘Tips and Tricks’ cards are relevant to residents who can brush their own teeth, who require assistance or who might refuse care. Care home staff will be asked to record daily tooth brushing on the ‘Weekly Oral Hygiene Record’ along with any ‘Tips or Tricks’ they used. The record will be used to assess fidelity of the intervention implementation.

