### Participant timeline

Figure 2 provides an overview of the feasibility study time schedule. At the allocation time point (t_−2_), recruited care homes will be randomly allocated to an intervention or control arm. At the enrollment time point (t_−1_), residents within the recruited care homes who are interested in taking part in the study will be asked to provide written consent to undergo two tests to determine their eligibility. If eligible, they will then be asked to provide informed written consent to take part in the feasibility study. The care homes allocated to the intervention arm will be asked to implement the oral health intervention based on the NICE guideline NG48 from baseline (t_0_) to the 12-month time point (t_2_), and the care homes allocated to the control arm will be asked to continue with their usual routine practice during the same 12-month period. Assessments (intervention and control group) will be undertaken at baseline (t_0_), 6 months after baseline (t_1_) and 12 months after baseline (t_2_). All assessments will take place at the care homes. More detailed information about the above processes is provided in the relevant sections below.

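### Two sections contradict each other on whether the dental examiners are blinded, and other arrangements could weaken that blinding

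*Protocol article*

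**What the plan says.** The section Who will be blinded accepts that care homes and residents cannot be blinded, but says that "the clinical dental examiners that will record the baseline and outcome measures will be". It adds that the statistician is blinded too, and gives one safeguard: "The care home staff will be instructed not to reveal allocation information to the dental examiners".

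The next section, Procedure for unblinding if needed, says: "The study design is open label with only the statistician being blinded".

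Three other sections bear on whether examiners could stay blind:

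- **Participant timeline.** Allocation comes first: at the earliest time point "recruited care homes will be randomly allocated to an intervention or control arm". Residents are enrolled and examined at baseline after that, and all assessments take place in the homes.
- **Who will take informed consent?** For the feasibility study, "written informed consent will be obtained from eligible care home residents by a research assistant or dental examiner".
- **Intervention description.** Staff training takes place "prior to the residents completing the baseline assessments". The staff OHAT is an intervention component, and "Administration will take place immediately prior to the initial dental assessment at baseline and at the 12-month follow-up visit". Intervention homes also receive a poster, cards and weekly hygiene records.

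**The concern.** Either the examiners are blinded or they are not. A site that follows the unblinding section has no reason to protect the examiners from knowing the arm. A reader who relies on the section before it will take the clinical outcomes as assessor-blind.

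This matters because nothing else is presented as blind at the point of assessment. EQ-5D-5L and OIDP are answered by unblinded residents to a research assistant whom the protocol does not list as blinded. Symptom diaries are kept by unblinded care staff. That leaves the examiner-recorded measures. Of these, visible plaque, bleeding on probing, caries and OHAT involve judgement; the number of teeth is a count with little room for observer bias.

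The Outcomes section expects the study to help choose a primary outcome and to supply estimates of treatment effect for the definitive trial. The statistical methods section plans 95% confidence intervals for between-arm differences. An examiner who knows the arm could shift those differences.

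**Working it through.** No arithmetic applies, because no figure in the document depends on this point. The check sets the sections side by side.

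**1. Who is blinded.**

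| Role | Who will be blinded | Procedure for unblinding if needed |
|---|---|---|
| Care homes, residents | No | No (open label) |
| Dental examiners | Yes | No (only the statistician is) |
| Statistician | Yes | Yes |

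The two sections disagree on the examiners and on no one else. Neither is a change log, and no analysis plan could make both true.

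**2. Could there be cues to the arm at the baseline examination?** The order is allocation, enrolment, then baseline, with staff training in intervention homes completed before baseline. So differences between arms can exist when the examiner first arrives. The staff OHAT is timed immediately before that examination. The Outcomes section collects fidelity data, including staff OHAT completion, from intervention homes only. The trial therefore introduces this step in one arm. Weekly brushing records are a weak cue here, because the intervention runs from baseline and few or none should yet be filled in.

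**3. Could there be cues at 12 months?** The staff OHAT is repeated at that visit. Whether the words placing it immediately before the examination extend to this visit is ambiguous; they clearly apply to the initial assessment. By then a year of records, posters and cards may be present in intervention homes, and the examiner works in the home.

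**4. Who takes consent.** The consent section allows a research assistant or a dental examiner. The recruitment section describes the research assistant providing the information sheet and asking for consent, and the implementation section has a research assistant enrol participants. An examiner taking consent would discuss the study with residents whose home is already allocated.

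**5. Reach of the safeguard.** Staff are told not to disclose. Residents are not blinded and are in direct contact with the examiner, but no such request to them is stated.

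Step 1 is a contradiction on the face of the text. Steps 2 to 5 show routes by which blinding could fail; none shows that it does.

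**The case against.** A reader might infer that the schedule reveals the arm: the staff OHAT happens before the examination in every intervention home and in no control home, so it identifies the arm perfectly. The document does not support that, for three reasons.

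- Nothing says examiners witness the staff OHAT or see its form, the care plan, the records or the poster, and staff are told not to disclose. A cue works only if it is noticed.
- Homes on either arm may keep their current practices, and routine practice is described as heterogeneous. Some control homes may carry out oral assessments of their own.
- The timing immediately before the examination is clear only for baseline.

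The consent point is also modest. The recruitment section refers the reader to the consent section, enrolment is not the same as consent, and taking consent need not disclose the arm. It is an avoidable exposure, not a breach.

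On weight, the study has no primary outcome, its analysis is limited to summary statistics and confidence intervals, and the listed feasibility measures (recruitment, retention, delivery, completion) do not depend on examiner blinding. A journal article may also leave visit logistics to the full protocol.

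These arguments limit the second part of the point and its priority. They leave the contradiction untouched: both statements are in the article, and the missing detail cannot reconcile them.

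**Conclusion.** The contradiction is established and should be corrected. The further threat to examiner blinding is a well-founded risk: the document supports saying that the arm could be revealed, not that it is.

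The outcomes exposed are those the examiners record at baseline and 12 months, chiefly plaque, bleeding, caries and OHAT. The consequence is possible observer bias in the between-arm estimates carried forward to the definitive trial. Its size cannot be derived from the document. The feasibility proportions are not affected.

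The conclusion assumes that the section dedicated to blinding states the sponsor's intention and that the sentence in the unblinding section is the slip. With no primary outcome and a descriptive analysis, this is a correction that should be made, not a flaw that invalidates the study.

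**What to change.** 1. **Procedure for unblinding if needed:** replace the statement that only the statistician is blinded with one that matches the section before it, for example: *Care homes and residents are not blinded; the dental examiners and the study statistician are blinded to allocation.* Keep the existing rule on when the statistician is unblinded.
2. **Who will take informed consent?** Remove the dental examiner as an alternative, so that consent agrees with the recruitment and implementation sections.
3. **Intervention description and Who will be blinded:** reconcile the two by stating that the staff OHAT and its forms, the care plans and records, and the posters and cards are kept out of the examiners' sight. This does not call for a new schedule for any intervention component.
4. **Non-disclosure:** extend the request to residents.
5. **Optional:** have examiners record which arm they believe the home is in at the 12-month visit, so that the workability of examiner blinding can be reported for the definitive trial.

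The cost is a few sentences, minor visit logistics and, if item 5 is adopted, one case report form question. The trial status section says recruitment has been postponed and has not begun, so the changes can be in place before any resident is examined.

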## Data collection and management

### Plans for assessment and collection of outcomes

#### Feasibility study

All study participants (intervention and control arms) will undergo an oral examination to collect clinical data. Participants will also provide self-report information on person-centred measures via interviewer-administered validated questionnaires and a symptom checklist. The following assessments will take place at the care home for each selected resident:

• Clinical outcomes will include the number of teeth, number of teeth with coronal and root caries lesions, the proportion of teeth with visible plaque and the proportion of teeth that bleed on probing. The dental examination will be undertaken at baseline and at 12 months by trained dental examiners, commissioned by the research team from the South Eastern HSC Trust, in Northern Ireland, and the Whittington Health Dental Services, in North London.

• A brief and practical assessment of the resident’s oral health needs. This will be assessed using the OHAT questionnaire [26]. The dental examiner will undertake this assessment at baseline and 12 months.

• Oral symptoms and urgent dental care: This refers to the number of reported episodes of dental pain, sepsis, discomfort and urgent dental care appointments. Care support staff using a checklist diary log will collect this information weekly. Research assistants will also collect this information at baseline, 6 months and 12 months.

• Health-related quality of life will be assessed through the EQ-5D-5L questionnaire [27]. This questionnaire will be administered by a trained research assistant to all participants at baseline, 6 and 12 months.

• Oral health-related quality of life will be assessed using the OIDP questionnaire [28]. This questionnaire will be administered by a trained research assistant to all participants at baseline, 6 and 12 months.

In addition, data will be collected at care home level (from the care home managers) for all participating care homes. Information will be collected at baseline and at 12 month follow-up and refers to the funding and organisational features of the care home; the number and overall demographic and health characteristics of residents; the number and oral health training of the staff; the provision of oral health programmes; and the arrangements for health care of the residents.

#### Process evaluation

Semi-structured interviews with care home staff and residents will be undertaken to assess the intervention’s feasibility and acceptability, and to explore how the intervention could be embedded in standard practice guided by Pfadenhauer et al.’s framework [21]. The interviews will last between 30 and 60 min and will be digitally recorded. Participants will be provided with the option to have the interview conducted in person at the care home or over the telephone. The interviews will be undertaken in accordance with a protocol consisting of semi-structured open-ended questions.

#### Cost-consequence model

Semi-structured interviews with key stakeholders will be undertaken to identify key outcomes including clinical and quality of life measures, resource use and measures of equity that are likely to inform decision-making. The interviews will be conducted in accordance with a protocol consisting of semi-structured open-ended questions and will last no longer than 20 min. The interviews will be conducted over the phone or in person and will be digitally recorded.

#### COVID-19

The coronavirus (COVID-19) pandemic has impacted excessively on care homes and raises many challenges for their safe operation and protection of the residents and staff. To ensure residents, staff and the research team are protected every precaution will be taken to minimise the risk of infection. Face-to-face visits will only be undertaken where care homes have been COVID-free for at least 14 days. Prior to each face-to-face visit, care homes will be asked to complete a COVID-19 screening questionnaire to assess and minimise any risk. Researchers will also provide a declaration of their own COVID status (no symptoms or contact with known COVID cases for 14 days). During each visit, researchers will wear a face mask, ensure social distancing and perform hand washing/hand sanitization.

### Plans to promote participant retention and complete follow-up

The research team will have regular contact with the recruited care homes throughout the study period. Care homes will be kept well informed of the study’s progress via a quarterly email.

